### 3.8 Response evaluation

The tumor reduction effect will be evaluated in cases that have lesions measurable by RECIST guidelines (version 1.1) to calculate the response rate. The rate of subjects for whom the best overall response is complete response (CR) or partial response (PR), is defined as the response rate .

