## (5) Time point response

The time point response will be determined at each image evaluation time point in accordance with the criteria specified in the table below based on a combination of the response of target lesions, response of non-target lesion, and incidence of new lesions.

When there are no non-target lesions at baseline, the overall response will be determined based on the response of the target lesion and incidence of new lesions, and when there are no target lesions at baseline, the overall response will be determined based on the response of non-target lesions and incidence of new lesions in accordance with the criteria specified in the table below.

Determination criteria for time point response (when target lesions are present).

| Response of target lesion | Response of non-target lesion | Incidence of new lesion | Overall response |
|---------------------------|-------------------------------|-------------------------|------------------|
| CR                        | CR                            | No                      | CR               |
| CR                        | Non-CR/Non-PD                 | No                      | PR               |
| CR                        | Not evaluated                 | No                      | PR               |
| PR                        | Non-PD or not fully evaluated | No                      | PR               |
| SD                        | Non-PD or not fully evaluated | No                      | SD               |
| Not fully evaluated       | Non-PD                        | No                      | NE               |
| PD                        | Any                           | Yes or No               | PD               |
| Any                       | PD                            | Yes or No               | PD               |
| Any                       | Any                           | Yes                     | PD               |

Determination criteria of time point response (when target lesions are absent).

| Response of non-target lesions | Incidence of new lesions | Overall response |
|--------------------------------|--------------------------|------------------|
| CR                             | No                       | CR               |
| Non-CR/Non-PD                  | No                       | Non-CR/non-PD    |
| Not fully evaluated            | No                       | NE               |

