The response rate is the rate of patients whose best overall response {3.8(6) Best overall response} in a target population with measurable lesions is CR or PR as a proportion of all the cases that underwent treatment.

(7) Health-related quality of life (HRQoL)

See "5.5 Survey of health-related quality of life".

(8) Adverse events (toxicity)

Adverse events that are observed from registration to the discontinuation of the protocol treatment will be evaluated in all treated cases (see "19 Evaluation and reporting of adverse events").

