## 5.10 Method of analysis and assay

(1) Definition of population to be analyzed

The analysis set is defined as below:

Total eligible cases: "Total eligible cases" is defined as a group of patients that overlapped and error registrations are removed from patients who registered in accordance with "5.2 Registration of cases".

Total treated cases: "Total treated cases" is defined as a subgroup of patients among the total eligible cases who received scheduled treatment at least once daily.

(2) Outcome measures

Outcome measures in this study are defined as below:

① Primary outcome measures

- Clinical benefit rate (CBR)

② Secondary outcome measures

- Progression free survival (PFS)
- Overall survival (OS)
- Time to treatment failure (TTF)
- Time to chemotherapy (TTC)
- Response rate (RR)
- Health-related quality of life
- Adverse events (toxicity)

(3) Analysis plan

① Primary analyses

Whether CBR, the primary outcome measures, exceeds 30% will be examined using accurate tests based on binomial distribution and the corresponding 90% confidence interval by cohorts with the entire secondary endocrine therapy. Meanwhile, the analysis set includes all treated cases, and a significance level of 5% is set for 1-sided tests.

② Other analyses

Analysis of the interaction effect of CBR is conducted for responsiveness to the primary endocrine therapy, expression intensity of ER, and presence or absence of PgR expression for all registered cases to examine the significance of effect predictors of the secondary endocrine therapy. The following classification will be used for each factor:

A) Responsiveness to the primary endocrine therapy

- Very low sensitivity group: Recurrence at less than 2 years after the initiation of postoperative endocrine therapy, or progression at less than 3 months after the primary therapy for metastatic breast cancer [corresponding to the ‘very low’ group of Figure 1 in 4.2 (2)].
- Low sensitivity group: Recurrence at 2–5 years after the initiation of postoperative endocrine therapy, or progression at 3–9 months after the primary therapy for metastatic breast cancer [corresponding to the ‘low’ group of Figure 1 in 4.2 (2)].

B) ER expression intensity

- ER low group: ER slightly positive (J-score classification is 1–9%)

- ER high group: ER positive (J-score classification is 10% or higher)

C) Presence or absence of PgR expression

- PgR negative group: PgR negative (J-score classification is negative)

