- PgR positive group: PgR positive (J-score classification is 1% or higher)

Analyses of secondary outcomes will also be conducted on a by-cohort basis. For RR defined by a 2-value endpoint response, an accurate 90% confidence interval based on point estimation and the binomial distribution is calculated. Furthermore, for PFS, OS, TTF, and TTC, which are time-to-event outcomes, a survival curve will be estimated using a Kaplan-Meier method, and 90% confidence intervals of the survival rate at each event will be calculated using Greenwood's formula. The interaction effect will be analyzed for effect predictors in the same manner as that used for the primary outcomes.

Analysis of adverse events will be performed in all treated cases. Incidence rate by types and grade will be calculated for reported adverse events.

③ Analysis of HRQoL

FACT-G, Breast, and ES, which are calculated as total scores, will be calculated for the aggregate score and subdomain scores in accordance with a scoring manual to calculate the fundamental statistics at the time of each survey for all subjects.

Furthermore, cases with decreases in scores exceeding the threshold values as compared with scores at the registration will be individually identified and the maintenance rate of QoL will be calculated using MIDs identified by scales as a meaningful threshold value of decrease of QoL score at each measurement point.

Information obtained from questions about changes will be used as subjective anchoring information required for the identification of MID during the endocrine therapy, and differences from the previously established MID will be examined.

Since it is considered that the evaluation and analysis of HRQoL have no influence on the clinical benefit rate, which is the primary outcome measures of this study, analysis will be implemented immediately after the data collection (after the collection of QoL questionnaires at 3 months for the last registered case). The results of the analysis will be published as conference presentations and papers.

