### 6.2 Inclusion criteria

Cases that satisfy all of the following conditions are included in this study as subjects.

- (1) A patient with estrogen receptor (ER) positiveNote 2 postmenopausalNote 3 breast cancer who is histologically diagnosed as breast cancerNote 1.

Note 1: No distinction is made according to the tissue subtype of cancer.

Note 2: Determination of ER is based on the determination of the primary focus of the breast in accordance with the definition of ER positive that is detailed in section 3.6. In this regard, a case in which evaluation of the primary focus is difficult and which is determined as ER positive based on evaluation of a metastatic lesion can be registered. Furthermore, when the results of evaluation differ between the primary focus and metastatic lesion, the result of the primary focus will be considered for the evaluation of ER expression.

Note 3: At least 1 of the following conditions regarding menopause should be satisfied.

- ① Aged 60 years or older
- ② Younger than 60 years and absence of menstruation for the past 1 year or longer (without hysterectomy)
- ③ Had bilateral oophorectomy

When the presence or absence of menopause of the subject is unclear, FSH and plasma estradiol levels will be measured to confirm whether these are at the after menopausal level as defined by the criteria of each facility.

- (2) Diagnosis of breast cancer corresponds to either of the following. No distinction is made according to the presence or absence of measurable lesions.

- ① Stage IV breast cancer associated with distant metastasis that cannot be a candidate for surgery at the first visit.  
(See 3.3 Classification of clinical stages)
  - ② Breast cancer associated with progression or recurrence caused by distant metastasis after initial treatment (after surgery and treatment before or after the surgery) for breast cancer aiming at curing. However, local recurrence for which radical excision is applicable (this represents the chest wall surrounded by the lower edge of the clavicle as the upper limit of surgical site, the costal arch as the lower limit, the midline of the sternum as interior limit, and the anterior edge of the latissimus dorsi muscle as the outer limit) is excluded.
- (3) Endocrine therapy for metastatic breast cancer is planned.
- (4) Performance status (PS) of ECOG is 0 or 1 Note 4.  
(See 3.5 Evaluation of Performance Status (PS))

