### 7.3 Sample size determination

This study is an observational study, in which therapy is selected based on the preferences of medical staff and patients. The study does not aim to compare different cohorts. To test the major study hypothesis, the threshold clinical benefit rate is set as 30%, and the expected clinical benefit rate is set as 50% in each cohort. Assuming the use of an accurate binomial test, it is estimated that the required number of cases is 43 under a condition of  $\alpha=0.05$  (one-tailed) and  $\beta=0.2$ . Assuming a dropout rate of about 10%, the target sample size estimated to be required for each cohort was set at 50. This study is an observational study, and cases will not always be evenly distributed to each cohort. However, it is needed to set the sample size corresponding to the 4 groups at a maximum [(4) Selection of drugs]. Therefore, a target case quantity of at least 200 was set. Meanwhile, registration will continue until all 4 groups achieve the target number of 50 cases per group within the time frame set for registration, even after a total registration number of 200 cases is achieved.

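### Section 3.9 (6), read literally, counts responders only among patients with measurable lesions but divides by all treated cases, which does not match the measurable-lesion population in section 3.8

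*Protocol*

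**What the plan says.** Four places in the protocol bear on the response rate.

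- **Section 3.8 (opening paragraph).** Tumor reduction "will be evaluated in cases that have lesions measurable by RECIST guidelines (version 1.1) to calculate the response rate". The rate is then defined as the rate of subjects whose best overall response is CR or PR. No fraction is written out, but the restriction implies measurable-lesion cases as the base.
- **Section 3.9 (6).** RR is the rate of patients whose best overall response "in a target population with measurable lesions is CR or PR as a proportion of all the cases that underwent treatment". This is the only place where a denominator is put in words.
- **Section 6.2 (2).** On eligibility: "No distinction is made according to the presence or absence of measurable lesions". Patients with only non-measurable disease are therefore enrolled.
- **Section 5.10.** Total treated cases are "a subgroup of patients among the total eligible cases who received scheduled treatment at least once daily", with no condition on measurability. For the analysis: "For RR defined by a 2-value endpoint response, an accurate 90% confidence interval based on point estimation and the binomial distribution is calculated". This is done by cohort, and no denominator or analysis set is named for RR.

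Section 3.8 (5) also matters. For patients without measurable disease, "when there are no target lesions at baseline, the overall response will be determined based on the response of non-target lesions" and on new lesions. The table that follows allows CR, non-CR/non-PD, NE or PD. PR is not available.

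**The concern.** A response rate needs one population that governs numerator and denominator alike. Section 3.9 (6), taken at its word, uses two. A treated patient with only non-measurable disease stays in the denominator but cannot be counted as a responder, even if she reaches the CR that section 3.8 (5) allows her. The result is neither the response rate in measurable disease that section 3.8 points to, nor an all-treated rate in which every patient's response could count.

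The affected group is not hypothetical. Section 3.8 (1) classes bone lesions without a measurable soft-tissue component, effusions and previously irradiated lesions as non-measurable. Section 3.8 (4) has a progression rule for cases with only non-measurable lesions, and 3.8 (5) has a separate table for patients without target lesions.

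At stake is the reported value of a named secondary outcome and what its 90% confidence interval describes. An analyst following 3.8 and an analyst following 3.9 (6) would report different figures from the same data.

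**Working it through.** **The plan's own figure.** The protocol computes no RR figure. Its only computed design figure is 43 cases per cohort, in section 7.3, and it concerns CBR: "the threshold clinical benefit rate is set as 30%, and the expected clinical benefit rate is set as 50% in each cohort". The exact one-sided binomial test at 5% with n = 43 declares success at 19 or more patients with benefit, with actual type I error 0.0342 and power 0.820. So 43 reproduces. Allowing for 10% dropout, 43/0.9 = 47.8, or 48, which the protocol sets at 50. None of this depends on RR.

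**Inputs for RR**

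- T = treated cases in a cohort. The target of 50 in section 7.3 is used for illustration.
- M = treated cases with at least one measurable lesion, and m = M/T. Not given in the protocol; taken as 0.5 to 0.9.
- x = patients with measurable lesions whose best overall response is CR or PR. The protocol gives no expected RR; 20% among measurable cases is assumed, with 10% and 30% as alternatives.

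**Relation between the two rates**

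- Base implied by 3.8: RR(measurable) = x/M.
- Literal 3.9 (6): RR(literal) = x/T = (x/M) × (M/T) = RR(measurable) × m.
- Relative reduction: 1 − m, whatever the RR.

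With RR(measurable) = 20%: 0.6 × 0.20 = 12% and 0.8 × 0.20 = 16%. With 10% it would be 6% to 8%, and with 30% it would be 18% to 24%.

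**Exact (Clopper-Pearson) 90% intervals, cohort of 50, RR 20% among measurable cases**

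| m (assumed) | x/M | 90% CI | x/T | 90% CI |
|---|---|---|---|---|
| 0.5 | 5/25 = 20% | 8.2–37.5% | 5/50 = 10% | 4.0–19.9% |
| 0.6 | 6/30 = 20% | 9.1–35.7% | 6/50 = 12% | 5.4–22.3% |
| 0.7 | 7/35 = 20% | 9.8–34.3% | 7/50 = 14% | 6.8–24.7% |
| 0.8 | 8/40 = 20% | 10.4–33.2% | 8/50 = 16% | 8.2–27.0% |
| 0.9 | 9/45 = 20% | 10.9–32.3% | 9/50 = 18% | 9.7–29.3% |

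For all 200 patients at m = 0.7: 28/140 = 20% (14.6–26.4%) against 28/200 = 14% (10.1–18.7%).

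**Interval width at m = 0.7, cohort of 50.** 34.3 − 9.8 = 24.5 points against 24.7 − 6.8 = 17.9 points; 24.5/17.9 = 1.37, so the measurable-case interval is about 37% wider.

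**The case against.** The best reply is that section 3.9 (6) is one awkward sentence with a harmless reading. The reference to a population with measurable lesions may govern the whole rate, and the closing phrase may mean only that every treated case within that population counts, including those not evaluable. On that reading 3.8 and 3.9 (6) agree. The reading is possible, but the sentence does not state it, the literal reading is at least as natural, and no other section decides. The same edit is needed either way.

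Several stronger claims are tempting and should not be made.

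- *That the protocol writes two conflicting denominators.* Only 3.9 (6) writes one. The base in 3.8 is implied by its restriction to measurable cases.
- *That patients without measurable lesions cannot respond by definition.* Section 3.8 (5) lets them reach an overall CR. It is the 3.9 (6) numerator that leaves them out.
- *That the literal rate is a biased estimate with an invalid interval.* Objective responses in measurable disease per treated patient is a definable proportion, and an exact binomial interval is valid for it. It is a different quantity from the rate in section 3.8; the fault is that the protocol does not hold to one of them.
- *That comparisons between drug cohorts are distorted.* Section 7.3 says the study does not aim to compare cohorts, and no measurable share is given for any of them. What stands is narrower: RR is reported by cohort, and 5.10 (3) extends the effect-predictor analysis to secondary outcomes. If m differed between such groups, differences in the literal RR would partly reflect measurability.

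The objection on precision is fair in absolute terms, because 37% wider is not slight. Much of the difference is scale, however. Dividing the literal interval at m = 0.7 by 0.7 gives 6.8/0.7 = 9.7% to 24.7/0.7 = 35.3%, close to the measurable-case interval of 9.8–34.3%. The literal interval is narrower mainly because the rate is lower, not because it says more about response in measurable disease.

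**Conclusion.** The point holds as a mismatch in a stated definition. As written, 3.9 (6) restricts the numerator to measurable disease and leaves the denominator at all treated cases, in a study that enrolls patients without measurable lesions. Followed literally, it returns the 3.8 rate multiplied by m. For m between 0.5 and 0.9, the reported figure falls by 50% to 10% in relative terms.

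The algebra is certain, but the size in this study is not. The 12–16% illustration rests on two assumptions that the protocol does not supply: 60–80% of treated patients with measurable lesions, and a 20% RR among them.

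RR is a secondary outcome with no threshold test and no sample size attached. The correction should be made before RR is analyzed, but nothing in the primary CBR analysis or in the 43 and 50 per cohort changes.

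**What to change.** In 3.9 (6), define RR as the number of treated patients with at least one measurable lesion at baseline whose best overall response is CR or PR, divided by the number of treated patients with at least one measurable lesion at baseline. State that patients rated NE remain in the denominator, and remove the reference to all treated cases. Write the same denominator into the opening paragraph of 3.8, and name it in 5.10 (3) as the analysis set for RR, so that the three sections agree.

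No new data are needed. Under 5.7 (2), the report of initiation of protocol treatment already records target, non-target and non-measurable lesions at baseline.

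The cost is a smaller denominator and a wider interval. For a cohort of 50 with m = 0.7 and RR 20% (assumed), the 90% interval becomes 9.8–34.3% instead of 6.8–24.7%. Reporting the number of treated patients without measurable lesions in each cohort alongside the RR would let readers see how many fall outside it.

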## 4 Objectives and significance of the study

### 4.1 Objectives of the study

The objectives of this study are:

- (1) To evaluate the efficacy and safety of secondary endocrine therapy in general as well as that of specific drugs in estrogen receptor-positive, HER2-negative postmenopausal metastatic breast cancer for which primary endocrine therapy had no favorable clinical effect (low sensitivity to primary endocrine therapy).
- (2) To clarify the effect of reactivity to the previous endocrine therapy (the period from the start of postoperative endocrine therapy to recurrence) and the biological characteristics of any given tumor (expression intensity of ER and presence or absence of PgR expression) on the results of the secondary endocrine therapy, and to obtain information to complement Hortobagyi's therapeutic algorithm.

### 4.2 Background inspiring this study

#### (1) Target disease

According to the National Cancer Center, Center for Cancer Control and Information Services, the estimated annual number of Japanese females affected with breast cancer in 2011 was about 72,500, and the rate per 100,000 population was 110.5, showing that the breast was the organ most frequently affected with malignancy in females. The annual number of deaths due to breast cancer in Japan was 13,148 in 2013, which is the 5th leading cause of mortality following stomach, colorectal, lung, and pancreatic cancers.

The incidence of breast cancer in Japanese females is constantly increasing and ranks closely with colorectal cancer and lung cancer .

About 90% of patients who are diagnosed with breast cancer receive surgical excision of the primary focus; however, the remaining 10% of patients have obvious distant metastasis at the first visit.

The survival rate of breast cancer is good if the tumor is detected early and removed surgically. It is considered that the presence or absence of micrometastasis, which is clinically undetectable at the initial visit, has a decisive influence on the patient's prognosis. About 60% of patients who received surgery were cured, on the other hand, about 40% experienced a relapse .

The median prognosis for the life expectancy of patients whose breast cancer has developed metastasis and recurrence is 28 months, and achieving a cure of metastatic or recurrent breast cancer is difficult even with current treatment techniques.

#### (2) Treatment of target population

##### ① Goal of treatment for metastatic breast cancer

It is very rare to achieve a complete cure for breast cancer that is already associated with

inoperable distant metastasis at the first visit (Stage IV) and recurrent breast cancer caused by distant metastasis; therefore, the major purposes of treatment are alleviation of symptoms, life extension, and maintenance and improvement of quality of life (QoL) in such cases . Metastatic breast cancer is mainly treated by drug therapy. Radiotherapy, surgical therapy, etc. are also used in combination as needed. These treatments are intended to provide alleviation of symptoms and maintenance of daily life.

② Endocrine therapy for metastatic breast cancer

The selection of therapies based on the biological characteristics of individual cancers has been emphasized in the medical treatment of breast cancer in recent years. Breast cancer has several subtypes, which are determined based on the expression of estrogen receptor (ER) and human epidermal growth factor receptor type2 (HER2) by the tumor, which are important prognosis predictors as well as effect predictors for endocrine therapy, chemotherapy, and molecularly-targeted agents; therefore, selection of therapy based on the subtype classification is implemented.

Furthermore, an algorithm proposed by Hortobagyi is implemented in clinical practice as a treatment strategy. For ER-positive metastatic breast cancer, treatment usually begins with an endocrine therapy and moves to different treatments as soon as the first therapy loses its efficacy, if there is no distant metastasis threatening the life prognosis. For cases responsive to the primary endocrine therapy, it is fundamental to continue endocrine therapy because the antitumor effect of the secondary endocrine therapy can be still expected even if the primary endocrine therapy loses its efficacy .

③ Recent outlooks regarding sensitivity and tolerance to endocrine therapy

Recently, several classification models regarding sensitivity and tolerance to endocrine therapies have been proposed as the basis of the clinical course associated with initial endocrine therapy.

The 2nd International Consensus Guidelines for Advanced Breast Cancer (ABC2), which was held as an international consensus conference for recurrent breast cancer, proposed classifications of resistance to endocrine therapies for ER-positive metastatic breast cancer according to the period from the start of initial endocrine therapy to recurrence or progression as below :

[Primary endocrine therapy resistant breast cancer]

- Cases that showed recurrence within 2 years after the initiation of postoperative adjunct endocrine therapy.
- Cases that showed progression of the disease condition within 6 months after the start of initial endocrine therapy for metastatic breast cancer.

[Secondary endocrine therapy resistant breast cancer]

- Cases that showed recurrence within 2 years after the initiation of postoperative adjunct endocrine therapy or within 12 months after the completion of the endocrine therapy.
- Cases that showed progression of the disease condition within 6 months after the start of initial endocrine therapy for metastatic breast cancer.

In addition, a classification scheme based on drug sensitivity that categorizes cases that show recurrence within 2 years after the initiation of postoperative adjunct endocrine therapy and cases that show progression within 3 months after the start of initial endocrine therapy as "very low" drug sensitivity, and cases that show recurrence after 2 years from the initiation of postoperative adjunct endocrine therapy as "low" drug sensitivity has also been proposed (Fig. 1) .

[figure not shown]

Figure 1: Classification of recurrent breast cancer according to its sensitivity to endocrine drug treatment as proposed during the ABC2 consensus conference

